### Data Collection

#### Participants’ Experience and Feedback

This study used two distinct questionnaires to assess the participants’ perspectives toward the usability of the Immersive Reality Training System (IRTS) for dental extraction training, which were designed based on previous research [44]. The Clinical Virtual Evaluation Questionnaire is structured to gather participants’ feedback on interactive education facilitated through simulator training (Multimedia Appendix 4). This questionnaire assesses three key parameters: experience and reliability (questions 1-9), knowledge (questions 10-14), and side effects (question 15). The questionnaire comprises 15 statements, which respondents assess using a Likert scale ranging from 1 (strongly disagree) to 5 (strongly agree). Conversely, the Immersive Reality Neuroscience Questionnaire will assess the system’s authenticity, the participants’ experiences, and the occurrence of cybersickness (Multimedia Appendix 5). This assessment will concentrate on four principal parameters: user experience (questions 1-5), game mechanism (questions 6-10), in-app assistance (questions 11-15), and IR-induced symptoms and effects (questions 16-20). The questionnaire is composed of 20 questions, which participants will answer using a Likert scale ranging from 1 (extremely poor) to 7 (extremely good). To ensure that the system’s quality is deemed suitable for use without causing significant cybersickness, each parameter must meet a minimum threshold (cutoff) score of 25 [45].

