#### Exclusion Criteria

Individuals who are unable to provide informed consent, possess health complications, display symptoms of cybersickness (eg, dizziness, disorientation, or vomiting) during training sessions, or are unable to complete the training session are excluded from participation. Additional exclusion criteria encompass a history of hallucinations, panic attacks, seizures, phobias (including claustrophobia and acrophobia), or active alcohol or substance abuse.

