#### Adverse Events

Participants who report feeling nauseated, dizzy, or disoriented, or having other health problems during a training session, will immediately be excluded from the activity. All such complaints will be recorded as cybersickness, and the occurrence of the condition will be noted for future evaluation.

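### The INRQ cutoff of 25 is biased towards passing on its cybersickness parameter, because students who become cybersick in training are excluded and nothing provides for their scores

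*Protocol article*

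**What the plan says.** Under Participants' Experience and Feedback, the protocol article describes the INRQ as 20 items, each scored 1 to 7 with 7 best, in four parameters of five items. Three cover user experience, game mechanism and in-app assistance. The fourth, questions 16 to 20, covers symptoms induced by the system. The section then sets a decision rule: for the system to be "deemed suitable for use without causing significant cybersickness", "each parameter must meet a minimum threshold (cutoff) score of 25".

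Three other sections bear on who supplies that score:

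- **Exclusion Criteria** lists, among those excluded from participation, people who "display symptoms of cybersickness" during training and people who cannot complete the session.
- **Adverse Events** says that participants who report nausea, dizziness, disorientation or other health problems in a session "will immediately be excluded from the activity". It adds that these complaints are recorded as cybersickness and noted for later evaluation.
- **Inclusion Criteria** already screens out anyone who cannot manage 10 minutes of virtual content in a head-mounted display (HMD).

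Table 1 places randomization before training and ticks satisfaction with the system at closeout only. The article does not say whether a student who stops for symptoms still completes the INRQ, or whether 25 applies to each person or to a group mean.

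**The concern.** The symptom parameter is there to detect cybersickness. The students whose scores would fall lowest on it are those who felt ill enough to be taken out of training. If they leave without completing the form, the score describes only those who tolerated the headset, and the rule is read in a group selected for not having the problem.

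This selection differs from eligibility screening. The 10-minute requirement defines who may enter. Cybersickness in a training session arises after randomization and is a result of using the system, so it is part of what the rule is meant to judge.

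The trial is a pilot that sets out to explore feasibility, and tolerability is a main part of that. The system could meet the stated cutoff while the separate cybersickness record shows that a number of users had to stop, and the article gives no instruction to read the two together.

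**Working it through.** **Inputs from the article.** Five items per parameter, each 1 to 7; cutoff 25; IR arm 15 per center in three centers, so 15 × 3 = 45.

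**What 25 means.** The range is 5 × 1 = 5 to 5 × 7 = 35. The cutoff is an item mean of 25/5 = 5.0, and lies (25 − 5)/(35 − 5) = 2/3 of the way up the range. The article takes the cutoff from a cited source and gives no derivation, so there is no figure to reproduce.

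**Assumptions.** The article gives no cybersickness rate, INRQ mean or SD. Let *q* be the share of IR students excluded for symptoms, *c* the completers' mean on the symptom parameter, and *s* the mean that the excluded students would have given. Take 25 as a group mean for now.

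**Step 1: mean over all exposed students**, *q·s* + (1 − *q*)·*c*, with *s* = 12 and *c* = 30:

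- *q* = 20%: 2.4 + 24.0 = 26.4 (passes)
- *q* = 30%: 3.6 + 21.0 = 24.6 (fails)
- *q* = 40%: 4.8 + 18.0 = 22.8 (fails)

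After exclusion the mean is 30 in each case. That is simply the assumed completer score; the comparison shows only that the score after exclusion does not respond to *q*.

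**Step 2: share at which the verdict flips.** Setting the mixture equal to 25 gives *q*\* = (*c* − 25)/(*c* − *s*). For *c* = 30 and *s* = 12 this is 5/18 = 27.8%; for *c* = 28 it is 3/16 = 18.8%. Over a wider range:

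| Completer mean *c* | *s* = 5 | *s* = 10 | *s* = 12 | *s* = 15 | *s* = 20 |
|---|---|---|---|---|---|
| 26 | 4.8% | 6.3% | 7.1% | 9.1% | 16.7% |
| 28 | 13.0% | 16.7% | 18.8% | 23.1% | 37.5% |
| 30 | 20.0% | 25.0% | 27.8% | 33.3% | 50.0% |
| 32 | 25.9% | 31.8% | 35.0% | 41.2% | 58.3% |

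Below these shares the system passes with or without the excluded students. If completers themselves average below 25, it fails either way.

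**Step 3: chance of passing the symptom parameter.** Normal approximation, 45 in the IR arm, SD 5 and *s* = 12 (both assumed):

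| *c* | *q* | Completers only | All exposed |
|---|---|---|---|
| 28 | 10% | 1.00 | 0.95 |
| 28 | 20% | 1.00 | 0.39 |
| 28 | 30% | 1.00 | 0.004 |
| 26 | 10% | 0.90 | 0.23 |
| 26 | 20% | 0.89 | 0.01 |
| 25 | 10% | 0.50 | 0.03 |
| 24 | 10% | 0.10 | 0.001 |

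One row by hand: at *c* = 28 and *q* = 20%, 9 of 45 are excluded. The all-exposed mean is (36 × 28 + 9 × 12)/45 = 24.8, with standard error 5/√45 = 0.745. Then z = (24.8 − 25)/0.745 = −0.27, and the chance of reaching 25 is 0.39.

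**Step 4: if 25 is a per-person cutoff.** Let *p* be the proportion of completers reaching 25. If none of the excluded students would reach it, the proportion over all exposed is *p*(1 − *q*). Scoring completers only reports *p*, so the bias has the same direction.

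**The case against.** The strongest case on the other side has five parts.

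- **A pass is not secured by design.** A reader might infer that the exclusion makes the rule almost certain to pass. The article does not support that. An item mean of 5 out of 7 is a fairly demanding bar: only 16.2% of uniformly random five-item answer patterns reach it. All four parameters must reach 25, and three of them do not measure symptoms. Under the assumptions of Step 3, the completers-only chance on the symptom parameter runs from about 1% (completer mean 23) to about 100% (28 or more). This objection stands in full.
- **The size is assumed.** The scores of 12 and 30 and the shares of 20% to 40% are not in the article, and the 10-minute HMD screen may keep the true share low. This stands; it is why the working gives a range and no single estimate.
- **The missing scores are inferred.** Adverse Events speaks of exclusion from the activity, which could mean only the session, and Table 1 does not name the INRQ in its satisfaction row. This stands as a caution. But Exclusion Criteria speaks of exclusion from participation, and the article nowhere provides for a form from those who stop.
- **Cybersickness is captured elsewhere.** Complaints are recorded, and the Clinical Virtual Evaluation Questionnaire has a side-effects item. The information is therefore kept, but the stated rule does not use it.
- **Completers can still report symptoms.** Complaints not voiced in the session, or starting after it, can lower questions 16 to 20. The parameter stays informative, but about a selected group.

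The handling of stopped participants might be set out in a fuller document. The point does not rest on that omission: the cutoff, its purpose and the exclusion are all stated here, and together they push the symptom score one way.

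**Conclusion.** The concern holds as one of direction. On the natural reading, the cutoff is biased towards passing on the symptom parameter, because students who become cybersick or cannot finish training are excluded, their scores are not provided for, and the cybersickness record is not tied to the cutoff.

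The size cannot be stated from the article. With symptomatic students at 12, exclusion turns a fail into a pass only above about 28% symptomatic if completers average 30, and above about 19% if they average 28. In the planned arm of 45 that means at least 13 students (27.8% of 45 is 12.5) or at least 9 (18.8% of 45 is 8.4). With completers below 25 the exclusion does not change the verdict. These figures rest on the assumed scores and on reading 25 as a group mean.

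Two stronger conclusions do not follow: that the rule is bound to pass, and that the intolerance data are lost. The point is still worth correcting, since the rule supports a statement about tolerability and the correction is cheap.

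**What to change.** 1. Apply the cutoff to all IR-arm students who put on the HMD. Those who stop complete the INRQ when they stop.
2. State whether 25 is a per-person cutoff or a group mean.
3. Beside the cutoff result, report the number stopped for symptoms over all exposed (planned 45), with a 95% confidence interval. For centers already run, take this number from the cybersickness record described under Adverse Events. The article reports 60 students enrolled at two centers, which at 15 per arm is 30 in the IR arm, so collection at stopping may be possible only for the 15 planned at the third center.
4. Where the form of a student who stopped is missing, count that student as not meeting the cutoff in the per-person proportion. A missing form cannot be averaged, so show the mean under a stated low score as a sensitivity analysis.

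The cost is some wording, a 20-item form for the few who stop, and a result that may look less favorable. No change to when or why training is stopped is proposed.

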#### Participants’ Performance and Knowledge Improvement

To assess the practical skills and knowledge acquired, participants from both the intervention and control groups will be required to complete a pretest prior to the training and a posttest following the training session. The MCQs were administered in accordance with the reference textbook used by the Faculty of Dentistry, as outlined in the dentistry curriculum [46]. The scores ranged from 0 to 100, and the test scores of both groups were subsequently compared. The MCQs are centered on the procedural steps, instrumentation, and guiding principles pertinent to dental extraction. This examination is an established component of the curricula at Hasanuddin University, Padjajaran University, and Universitas Sumatera Utara, aimed at assessing students’ practical competencies and theoretical knowledge. Consequently, a comparative analysis test will be used to evaluate the scores obtained from the clinical skill training between these two groups.

Additionally, the performance of participants will be evaluated through recorded video training and will be assessed by an independent reviewer, focusing on training time completion, in-app lag or confusion, and skipped steps. The confidential paper-based data of participants will be securely stored in a locked storage unit at the study site, while electronic data will be maintained in a protected folder on a server at Hasanuddin University, Makassar, Indonesia.

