**Conclusions:**

IR-based training offers a novel approach that may boost motivation, knowledge retention, and skill transfer in dental education. This pilot protocol explores IR’s feasibility and potential to advance dental students’ competencies.

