### Trial Design and Study Population

#### Overview

This protocol is for a prospective multicenter randomized clinical trial, which began in March 2025 and is expected to end in November 2025. This protocol outlines our plan to assess the knowledge and skill enhancement of a pilot intervention across three centers: Hasanuddin University (Makassar, Indonesia), Padjajaran University (Bandung, Indonesia), and Universitas Sumatera Utara (Medan, Indonesia). A total of 90 dental students participated in the study (G*Power effect size 0.6, statistical power 85%). All participants enrolled in this study were randomly assigned to either an intervention group (n=15) or a control group (n=15) within each center. We used the block randomization method for the allocation of participants.

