#### Blinding and Calibration of Reviewer

Two independent reviewers (an oral and maxillofacial surgeon) were assigned to evaluate and score each participant’s pretest and posttest sheets (Multimedia Appendix 1). Before data collection, the assessors underwent a calibration session to standardize the answer key for the multiple-choice questions (MCQs) and ensure consistent scoring. During the study, the assessors were blinded to the participants’ identities and allocation status, as they did not have access to names or group assignments. A final score for each participant was calculated.

Additionally, the reviewer will assess the participants’ training videos, focusing on training time completion, in-app lag or confusion, and skipped steps, to evaluate participants’ performance during training.

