#### Intervention Group

Before the intervention, two oral and maxillofacial surgeons from each center will follow a comprehensive meeting held in Hasanuddin University, Makassar, to ensure consistent delivery of the interventions across centers and instructors. In addition, a facility assessment will be reported during the meeting to ensure that each center can deliver the intervention method using the same protocol.

Participants will be given a brief introduction and explanation of the study’s purpose. A research assistant will present the informed consent both in writing and verbally. This study has adopted standardized procedures for tooth extraction, using both open and closed methods.

The IR training session will be conducted in a standing position, where participants role-play as dentists. The training session will focus on open and closed dental extraction for the first molar tooth (tooth 46), supervised by two oral and maxillofacial surgeons in each center. For all training sessions, the first 10 minutes will be conducted under direct supervision. Participants will then continue their sessions for the last 40 minutes using in-app assistance (sound, highlighted areas, and arrows) without additional support for the remaining session.

The IR HMD wirelessly streams to an external device and will be used during the first session to monitor the participants’ training execution and provide guidance when necessary. Participants were required to complete a full round of training. This procedure included several steps: administering local anesthesia, making an incision and separating the tooth (in open method extraction mode), luxating and extracting the tooth, performing curettage, irrigating the wound, and suturing.

Following the completion of the procedure, participants are presented with the option to either restart the training sessions by selecting the reset button or terminate the session by choosing the exit button located in the menu area.

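### The article describes its between-arm comparison as one of skill, but the only outcome stated for both arms is a written multiple-choice knowledge test, and the training videos cannot supply the missing skill measure.

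*Protocol article*

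**What the plan says.** The Overview under Trial Design and Study Population sets the aim: "This protocol outlines our plan to assess the knowledge and skill enhancement of a pilot intervention across three centers". The section Participants' Performance and Knowledge Improvement gives the instrument: "To assess the practical skills and knowledge acquired, participants from both the intervention and control groups will be required to complete a pretest", with a posttest after the session. On the content of that test it says: "The MCQs are centered on the procedural steps, instrumentation, and guiding principles pertinent to dental extraction". Scores run from 0 to 100. The same section adds that the exam is an established part of the curriculum at the three universities and is meant to assess practical competencies as well as theory. It concludes that "a comparative analysis test will be used to evaluate the scores obtained from the clinical skill training between these two groups".

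The assessment rows of Table 1 are the MCQ, knowledge improvement by posttest score, and satisfaction with the Immersive Reality Training System (IRTS). Both questionnaires under Participants' Experience and Feedback concern that system.

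Videos of the training are also rated, "focusing on training time completion, in-app lag or confusion, and skipped steps". The section Blinding and Calibration of Reviewer describes the assessors of the test sheets as blinded because "they did not have access to names or group assignments". The videos follow in a separate paragraph, with no masking described.

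**The concern.** A written test of which steps, instruments and principles apply to an extraction measures what a student knows about the procedure. Whether the student can luxate a tooth or place a suture is a different construct. The aim and the comparison sentence put both under the word skill.

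What is at stake is the conclusion. If the MCQ scores differ between arms and the article's wording is followed, the report would say that one form of training produced better clinical skill. Readers could take that as evidence about manual extraction competence, which the trial does not test once the guided session is over. The comparison is inferential (the Data Analysis Plan names a multivariate ANOVA at the 5% level), so the pilot label does not remove the problem. The video ratings might be offered as the missing skill evidence, so they need checking as well.

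**Working it through.** No figure in the plan bears on this point and no arithmetic applies. The check sets the statements side by side.

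**1. Where skill is promised.** The Overview names knowledge and skill enhancement as the aim. Participants' Performance and Knowledge Improvement ties practical skills to the pretest and posttest, and ties the between-group comparison to clinical skill training. Strengths and Limitations again speaks of students' skills in carrying out extractions.

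**2. What is measured in both arms.**

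| Measure | Both arms? | Performed task after training? |
|---|---|---|
| MCQ, pretest and posttest | Yes, stated | No, written |
| Clinical Virtual Evaluation Questionnaire | Concerns the IRTS | No, opinion scale |
| Immersive Reality Neuroscience Questionnaire | Concerns the IRTS | No, opinion scale |
| Training videos | Not stated | No, filmed during training |

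One measure is stated for both arms, and it is written. None of the three assessment rows in Table 1 is a performed task or a video rating.

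**3. Whether the videos can stand in for a skill outcome.** The conditions under which they are taken are as follows.

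- IR arm (Intervention Group): the first 10 minutes are directly supervised. The last 40 minutes run with "in-app assistance (sound, highlighted areas, and arrows") and no other support. On completing the procedure, a participant may reset and start again.
- Control arm (Control Group): a 10-minute lecture, then 40 minutes of hands-on work guided by two surgeons.

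Item by item:

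- *In-app lag* needs an app. A phantom session has none, so there is no control counterpart. Confusion could occur in either setting if the words in-app qualify only lag.
- *Skipped steps* can be counted in both arms, because the two sections list nearly the same sequence from local anesthesia to suturing. The count is taken while software prompts one arm and surgeons guide the other. Skill and type of guidance cannot be separated in it.
- *Completion time* has the same difficulty. In addition, the control session has a set length, and an IR participant may repeat the round.

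**4. Whether the stated blinding could cover the videos.** The means given is to withhold names and group assignments. That works for an answer sheet. It cannot hide whether a recording shows a virtual scene or a phantom, and a rater who scores in-app lag must know that the session is IR.

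**Result.** The MCQ supports a statement about knowledge. Nothing else described supports a between-arm statement about acquired skill.

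**The case against.** The strongest reply is the article's own: the exam is an established curricular component intended to assess practical competencies, and its items are in Multimedia Appendix 1, which is not shown. This must be acknowledged, but it does not carry the claim. Curricular use shows that faculties accept the exam. It does not turn a written answer into a performed task, and the content the article describes is knowledge about a procedure.

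A second reply is that the labels are mixed rather than uniformly wrong. Table 1 already says knowledge improvement, and the Abstract speaks of satisfaction and understanding. That stands. The defect is an inconsistency, and the fix brings the other sections into line with Table 1.

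A third reply concerns the videos, and it limits the point. A reader might infer that the plan compares video ratings between arms, that in-app lag is therefore undefined for every control, and that the trial relies on unblinded ratings. The article does not say so. It attaches the group comparison to test scores, describes streaming only from the headset, describes no filming of controls, and makes its blinding statement in the paragraph on test sheets. IR-only filming is a plausible reading, although the text says only participants. On that reading the MCQ is still the sole comparator, so the main point is unaffected.

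A reader might also infer that the trial plans to conclude on motivation and skill transfer, because the Abstract says IR training may "boost motivation, knowledge retention, and skill transfer in dental education". That sentence is hedged, and the next one speaks of feasibility and potential. The Abstract's Objective names neither. Nor can it be said that motivation goes unmeasured, since the questionnaire items are in appendices that are not shown.

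**Conclusion.** The point holds in this form: the aim and the comparison are worded as skill, while the only outcome stated for both arms is a written knowledge test. The videos cannot fill the gap, whether they cover one arm or both. Its size is one of scope: one two-arm outcome, no performed task scored after training, and three video items taken during guided training, of which in-app lag has no phantom counterpart.

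The verdict assumes that the MCQ is as the article describes it, a written test on steps, instruments and principles, and that no performed post-training test exists beyond what the article and Table 1 list. It does not depend on the arm scope of the videos, which is unclear. It does not say that the blinding claim for the test sheets is false, that video ratings will be compared between arms, or that conclusions on motivation are planned.

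**What to change.** - In the Overview and in Participants' Performance and Knowledge Improvement, state the between-arm objective and conclusion as the effect on MCQ knowledge score, not practical or clinical skill. Use the same term wherever the result is reported.
- State whether videos are recorded in the IR arm only or in both arms.
- Report in-app lag for the IR arm only, as a usability measure.
- If completion time and skipped steps are collected in both arms, define them on the step list common to both. Present them as descriptive process measures of the guided session, not blinded by the means described, and not as evidence of acquired skill.

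The cost is wording and table layout. No new data or participants are needed, and the article reports data collection as still under way, so the change can precede analysis. The downside is a narrower claim: the trial would speak to knowledge of extraction, not to the ability to perform one.
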